### Outcomes

The feasibility of FRANI will be assessed by measuring outcomes related to adherence, acceptability, and usability as summarized in Table 2 (25, 26). According to the World Health Organization (WHO), adherence is “the extent to which a person's behavior – taking medication, following a diet, or executing lifestyle changes, corresponds with agreed recommendations from a health care provider” (27). Although there is no consensus in the literature on the best measure for adherence to eHealth technology interventions (25, 26), maximum benefit from the intervention as defined by creators should be considered (28). We define the sample adherent to FRANI if 70% or more of participants-days upload complete dietary recalls in the last two weeks of the pilot study. Acceptability summarizes likeability and satisfaction with FRANI, while usability summarizes what affects the use of the FRANI. Acceptability and usability are measured according to answers from structured questionnaires described in Table 3. If participants grade the acceptability or usability of FRANI as 30 or less points in their respective structured questionnaires, the app will be considered accepted or usable.

**Table 2 T2:** Domains and outcome measures for the FRANI pilot test.

Outcomes	Definition
Primary outcomes (feasibility)	
Adherence	The number of days participants upload completed dietary recalls on the FRANI divided by the total number of dietary recalls (complete + incomplete) of the last two weeks of the pilot test is equal to or higher than 70%
Acceptability	Summarizes likeability and satisfaction with FRANI according to answers from a structured questionnaire. If participants grade the acceptability of FRANI as 30 or less points on a scale from 10 to 50 points, the app will be considered accepted.
Usability	Summarizes possibility to use and intent to keep using FRANI according to answers from a structured questionnaire. If participants grade the usability of FRANI as 30 or less on a scale from 10 to 50 points, the app will be considered usable.
Secondary outcomes	
Percentage of meals recorded	The number of meals recorded on the FRANI divided by the number of total meals participants had during the last two weeks of the pilot test period.
Dietary Diversity Score^a^	Ranges from 0 to 10 points using MDDW dietary diversity food groups (daily score) measured in the first four weeks of the pilot study period.

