### Statistical analysis

The data from the pilot studies from Ghana and Vietnam will be analyzed and reported separately, though a pooled analysis will also be undertaken once both pilots have been completed. The analysis will be by intent to treat, and we do not expect to have loss of follow-up as this is a small scale pilot. Descriptive statistics and balance tables will be calculated for all variables and will be presented as medians or means with standard deviations. Differences in the outcomes between intervention and control groups will be estimated by multi-level Poisson regression models with the DDS and the SHDS as outcomes, a dummy variable for the treatment, a continuous time variable for the days and an interaction of treatment and time, and random effects at the individual level to account for the repeated measures. We will also undertake exploratory analysis for each food group of the DDS and the SHDS separately using odds ratio regressions. Socio-demographic variables that were not balanced after randomization will also be included in the robustness analysis.

A *p*-value < 0.05 will be considered statistically significant and *p*-value < 0.1 will be considered marginally significant. We will assess the need to screen outliers values greater than three standard deviations and will analyze the sensitivity of the treatment effect to the outliers.

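### The p<0.1 'marginally significant' label exempts no analysis, and no term, score or data set is named as the main effect; a null app has roughly an even chance of at least one labelled score-level result

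*Protocol article*

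**What the plan says.** All of the following is in the Statistical analysis section of the protocol article unless stated otherwise.

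- **Two thresholds.** "A *p*-value < 0.05 will be considered statistically significant", and a "p*-value < 0.1 will be considered marginally significant". Neither is limited to a subset of the analyses.
- **Three data sets.** The two countries will be "analyzed and reported separately, though a pooled analysis will also be undertaken once both pilots have been completed". The pooled set reuses the participants of both country sets.
- **Two scores.** The models are "multi-level Poisson regression models with the DDS and the SHDS as outcomes". Neither score is ranked above the other.
- **Two treatment terms per model.** Each contains "a dummy variable for the treatment, a continuous time variable for the days and an interaction of treatment and time", with random effects per individual. Neither term is identified as the test of effect.
- **Food groups.** There is also an "exploratory analysis for each food group of the DDS and the SHDS separately using odds ratio regressions".

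Table 2 (Outcomes) makes adherence, acceptability and usability primary and the two diet scores secondary. The Outcomes text adds that only secondary outcomes are compared between arms. The Sample size section says that the treatment effect size on both scores over the first four weeks will size a larger experiment.

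**The concern.** Because the primary measures are not compared between arms, every statement about what the app does to diet will come from these secondary and exploratory models. Each score in each data set yields two coefficients that could be reported as the effect, and any of them may carry a significance label up to p = 0.1. With 36 adolescents per country and a sample size set by budget, a labelled result is easy to obtain by chance. A reader could not tell from the protocol which result was meant to answer the question.

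A second problem lies in the model. With a continuous day variable and its interaction with treatment, the treatment coefficient is the arm difference where the day variable equals zero. That is not the effect over the four weeks, which is the period the Sample size section refers to. If it were read as the effect, the wrong quantity could be reported and carried into the next trial.

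**Working it through.** The protocol gives no power, effect size or familywise error rate, so there is no figure of its own to reproduce. The counts below come from its text.

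**1. Number of tests**

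- Score level: 2 scores x 3 data sets x 2 treatment terms = 12.
- Food groups: Table 2 gives ranges of 0-10 (DDS) and 0-14 (SHDS). Assuming one group per point, one treatment term per model and all three data sets, (10 + 14) x 3 = 72.

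**2. Expected labelled results with no true effect**

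The expected number is m x alpha. Correlation between tests does not change it, provided each test has its nominal error rate.

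| Tests | p<0.05 | p<0.1 |
|---|---|---|
| 12 score-level | 12 x 0.05 = 0.6 | 12 x 0.1 = 1.2 |
| 72 exploratory food-group | 72 x 0.05 = 3.6 | 72 x 0.1 = 7.2 |

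**3. Chance of at least one among the 12 score-level tests**

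This does depend on correlation, which the protocol does not give. If all 12 were independent, 1 - (1 - alpha)^12 gives 46% at 0.05 and 72% at 0.1. They are not independent, so null z-statistics were simulated. The countries were independent, and pooled z = (z_Ghana + z_Vietnam)/sqrt(2). Correlations were assumed between the two scores and between the treatment and interaction terms.

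| Score correlation | Treatment-interaction correlation | p<0.05 | p<0.1 |
|---|---|---|---|
| 0 | 0 (pooled overlap only) | 39% | 62% |
| 0.3 | -0.3 | 37% | 60% |
| 0.6 | -0.3 | 34% | 56% |
| 0.3 | -0.85 | 30% | 50% |
| 0.6 | -0.85 | 27% | 46% |
| 0.9 | -0.8 | 23% | 40% |

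Over the four middle rows the range is 27-37% at p<0.05 and 46-60% at p<0.1. The chance of three or more at p<0.1 in those rows is only 15-19%.

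If only the treatment term is read as the effect, there are 6 tests. With score correlation 0.3-0.6, the chance of at least one is 19-21% at p<0.05 and 34-37% at p<0.1.

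**4. What the treatment coefficient means**

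For a Poisson model with log link, with T the arm (0 or 1), t the day and u the individual effect:

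log E(Y) = b0 + b1 T + b2 t + b3 T t + u

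The log rate ratio between arms on day t is b1 + b3 t, so b1 alone is the difference at t = 0. Averaged over 28 days it is b1 + b3 x mean(t). If days are coded 1 to 28, mean(t) = (1 + 28)/2 = 14.5, and the average is b1 + 14.5 b3. If coded 0 to 27, it is b1 + 13.5 b3. An app that starts with no effect and builds up could have b1 near zero and a real average difference.

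**5. Sensitivity to the nominal-rate assumption**

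A rough normal approximation (18 per arm, 28 days, assumed mean score 4.5 and assumed variances) was used to see how a random-intercept Poisson model behaves at nominal 5%. The interaction rejected about 0.1% of the time when daily scores varied less than Poisson and individuals shared one slope. It rejected about 23% of the time when individual slopes varied strongly. For the treatment term the range was about 3% to 13%. The true rates could therefore be lower or higher than in steps 2 and 3.

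**The case against.** The case on the other side is substantial, and several parts of it stand.

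- **A reader might infer that a null app would probably yield several diet-score effects.** The documents do not support that. About one labelled score-level result is expected, and three or more is unlikely. A larger number comes from the food-group models, which the plan itself calls exploratory. They would give 3.6 expected results even at the ordinary 5% level, so the p<0.1 tier is not the sole cause.
- **A reader might infer that the loose label distorts the next trial's sample size.** It does not. The Sample size section uses the effect estimate, and no rule in the article ties a p-value to a go-ahead. What matters for sizing is which estimate is used.
- **A reader might infer that the plan lacks multiplicity control.** This is a condensed article and an analysis plan may exist unseen, so that absence is not a finding. Nor is strict error control over secondary outcomes in a pilot a settled requirement.
- **The tier is weaker, separate and declared in advance.** This is true: p<0.05 remains the only level called statistically significant. The gain from declaring it is limited, because the label still lets results between 0.05 and 0.1 be reported in the language of significance, for any analysis.

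What remains is what the article itself fixes: a p<0.1 label for everything, and a model with two treatment terms of which neither is the four-week effect.

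**Conclusion.** The point holds in a limited form, with minor to moderate severity. The p<0.1 label doubles the expected number of labelled null results at score level, from 0.6 to 1.2. It raises the chance of at least one from 27-37% to 46-60%. This rests on both treatment terms being read as effect tests, on nominal error rates, and on score correlations of 0.3 to 0.6 with treatment-interaction correlations of -0.3 to -0.85. More extreme correlation lowers the p<0.1 figure to about 40%, and no correlation beyond the pooled overlap raises it to 62%. The food-group addition of 7.2 against 3.6 rests on the counting assumptions stated above and concerns analyses already marked exploratory.

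Independently of these figures, the treatment coefficient in the stated model is a time-zero difference. The effect to report and carry forward should be the average difference over the four weeks.

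**What to change.** 1. Delete the sentence that creates the p<0.1 tier.
2. Designate the model-based average arm difference over the first four weeks as the main effect contrast, for example in DDS, from the pooled model with a country term, tested at two-sided 5%. State how days are coded, or define the contrast as an average over the 28 days so that coding does not matter. With one named test the nominal false-positive chance is 5%.
3. Report SHDS, the country-specific results and the treatment-by-time interaction as estimates with 95% confidence intervals.
4. Report the exploratory food-group odds ratios with intervals and no significance label.
5. State that the average four-week difference is the effect size to be used for sizing the larger experiment.

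The cost is wording only. Data collection and the fitted models stay as planned, apart from the country term in the pooled model if that example is adopted. The downside is that fewer results can be called significant. Deleting the tier alone would leave 0.6 expected score-level results at p<0.05, so step 2 is needed as well as step 1.

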### Data management

The data collected will be de-identified and stored on the computers of the institutions involved. Random numbers will be generated and linked to each participant, and they will be referred to exclusively by that participant code. The document linking both numbers will be destroyed once results of the study were published.

### Pilot test collaboration

The project is based on an interdisciplinary collaboration between the IFPRI, the Pennsylvania State University in partnership with the FAO, the University of Ghana, the Thai Nguyen National Hospital, the Thai Nguyen University of Medicine and Pharmacy, and the National Institute of Nutrition (NIN) of Vietnam. The principal investigator at IFPRI is responsible for coordinating the study, while the research teams based in Ghana and Vietnam recruit potential participants, send participants the informed assent and their parents the informed consent, answer questions and attend requests, and distribute the smartphones with the FRANI to eligible participants. The local research teams will also monitor participants throughout the study period, and report problems to the whole team. Because we do not anticipate negative outcomes for the participants, we have not established formal stopping rules nor an auditing conduct. The research team agreed on the final version of the pilot protocol. Weekly meetings are planned to report progress, verify deadlines, and manage the project. Any modifications in the protocol such as eligibility criteria, outcomes and analyses will be communicated to IFPRI and in-country IRBs when needed. The engineering team, based at the Pennsylvania State University, is responsible for data storage and the maintenance of FRANI. Members of all teams will be responsible for different parts of the results dissemination through journal articles, conferences and presentations.

## Discussion

This protocol describes a randomized controlled pilot study that will measure adherence, acceptability, and usability and determine the impact of an AI technology-based app in the quality of food choice of adolescent girls from Ghana and Vietnam. There is limited evidence on intervention studies that used technology to change eating habits (21). The FRANI technology has the potential to replace expensive and time-consuming questionnaires, and simplify and improve the precision of food consumption data collection. The pilot study will address gaps in the literature and advance the nutrition field by providing evidence on adherence, acceptability and usability of technology-based nutrition interventions, and by impacting the quality of food choice of adolescent girls in developing countries.

The pilot test of the FRANI is an important first step towards better quality, highly scalable data collection in nutrition and healthier food choices for a population at risk of malnutrition. The success of this intervention will depend on the use of the FRANI and the change in intake of nutritious and diverse foods. If the pilot and validation the FRANI technology are successful, the next steps in the development process include a larger randomized control trial to examine if technology-based nutrition intervention works for a more extended period of time.
